### Safety

The number of adverse events and related unexpected serious adverse events will be summarised descriptively by arm, grade and body system. The proportion of participants experiencing each toxicity will be summarised by maximum National Cancer Institute’s Common Terminology Criteria for Adverse Events grade^39^ experienced, overall and by arm. Operative RC complications will be graded using the Clavien Dindo classification.^40^

### Criteria for progression to the definitive phase III trial

The following guidelines for progression to a definitive phase III trial have been defined:The recruitment and follow-up rates must demonstrate that a definitive trial using similar procedures will achieve sufficient power to test the hypothesised difference between treatment arms.The sample size calculation for the feasibility study and proposed phase III trial are provided earlier. This assumes that 20% of all new diagnoses of NMIBC would be eligible and approximately 25% of those would be randomised. To proceed to a definitive trial, we need to show that at least 20% of eligible patients can be randomised.

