### Study aims

Our aims are to assess whether a larger phase III RCT is possible and to acquire sufficient 129 data to aid planning such a trial. Primary outcomes are: To assess the number of patients screened and identified as eligible within these six centres.To assess recruitment rates (number of patients randomised per month).

Secondary outcomes are:To assess acceptance of allocated treatment.To assess the rate of compliance with mBCG at 12 months after randomisation and collect reasons for non-compliance.To assess the feasibility and optimal frequency of collecting QoL data in patients treated for HRNMIBC.To obtain preliminary data on the QoL data of patients treated for HRNMIBC.To explore the reasons expressed by patients for declining recruitment into the study.

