### Sample size

The sample size for this feasibility study has been set to give confidence that the recruitment target for the main trial can be met. A formal power calculation is not appropriate as effectiveness is not being evaluated. It is estimated that, per year, over the six centres, there will be approximately 1000 new diagnoses of NMIBC, where 20% are likely to be eligible (200 patients).^31^ We would need to show that we are able to randomise approximately 25% of all eligible patients to be confident that the recruitment target for the main trial would be met within 3 years, with an additional nine centres. We therefore plan to recruit 60 patients over an 18-month period in the feasibility study. For the phase III trial, we anticipate either a single primary endpoint (cancer-specific survival) or coprimary endpoints (cancer-specific survival and averaged quality-adjusted life years (QALYs)). We estimate that 506 participants are required to have 80% power to show a superiority HR of 0.626 (based on an improvement in 5-year cancer-specific survival from 70% in the BCG arm to 80% in the RC arm), assuming a 3-year accrual period, 5 years of follow-up and accounting for 5% loss-to-follow-up.

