## Discussion

The 2015 NICE BC guidelines identified the comparison between mBCG and RC as one of their highest research priorities.^21^ This reflects the importance of this question but does not address how randomisation between two very different treatment options should occur or whether such a comparison is possible. Within this feasibility study, we are attempting to understand, address and develop methodology to allow such a comparison. This will require several key issues to be addressed. First, it is clear from other surgical versus non-surgical treatment trials^49^ that the most important element for RCT recruitment is keeping equipoise when discussing the treatment options by medical and nursing staff. While previous studies used research nurses to keep equipoise, this is not viable across many centres within the current research funding climate. In an attempt to replicate this model, we ran a number of educational days to train relevant medical and nursing staff about the importance of equipoise and to discuss their beliefs about HRNMIBC. All staff had opinions about the efficacy of BCG and QoL with RC, and so it was important to discuss these in an open forum to challenge these views and use evidence to dispel prior beliefs. We proposed a six-stage consultation plan to help staff keep patients at equipoise and so facilitate trial entry and treatment acceptance.^50^ Within this feasibility study, we will determine if this approach is possible and successful. Second, UK data do not accurately identify the number of patients with HRNMIBC, what proportion of these are suitable for both RC and mBCG and how many of these would accept randomised treatment options. Within this feasibility study, we will establish accurate data about the number of eligible cases across this population and understand what proportion accepts their randomised treatment allocation. We will use these findings to power the phase III comparative study. Finally, there are very few reliable data about QoL with mBCG and none that compare this directly to RC. Within this study, we will produce these data within 60 patients (30 for each arm) and so allow this endpoint to be modelled for the larger phase III study.

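### The only numeric progression condition (20% uptake) does not depend on eligible volume and, on the plan's own figures, does not secure recruitment of the 506-patient main trial

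*Protocol article*

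**What the plan says.** All references are to the protocol article.

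- **Study aims** names two primary outcomes: "To assess the number of patients screened and identified as eligible within these six centres" and "To assess recruitment rates (number of patients randomised per month". No target value is attached to either.
- **Sample size** expects, per year over the six centres, "approximately 1000 new diagnoses of NMIBC, where 20% are likely to be eligible (200 patients". It continues: "We would need to show that we are able to randomise approximately 25% of all eligible patients", in order to fill the main trial within 3 years with nine further centres. It then plans 60 patients in 18 months. The main trial needs 506 participants.
- **Criteria for progression to the definitive phase III trial** gives two guidelines. The first is "The recruitment and follow-up rates must demonstrate that a definitive trial using similar procedures will achieve sufficient power" to test the hypothesised difference; it states no rate, count or cut-off. The second recalls the 20% eligibility and 25% randomisation assumptions, then sets the requirement: "To proceed to a definitive trial, we need to show that at least 20% of eligible patients can be randomised".
- **Discussion** concedes that "UK data do not accurately identify the number of patients with HRNMIBC, what proportion of these are suitable for both RC and mBCG".

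**The concern.** Main-trial accrual is the product of two factors: how many patients are eligible, and what share of them is randomised. The numeric condition tests only the second. The first is a primary outcome, and the plan itself calls it poorly known, yet it enters the progression decision only through a guideline without a number.

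There is a second difficulty. The Sample size section ties success to about 25% of eligible patients, while the progression section accepts 20%. If neither figure, at the assumed volume, delivers 506 patients in the stated time, passing the threshold does not answer the question the study was set up to answer. The go or no-go decision would then rest on a judgement about rates made after they are known.

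**Working it through.** **Inputs (Sample size section):** 200 eligible per year over six centres; 60 patients in 18 months; 506 patients for the main trial; 3 years of accrual; 6 + 9 = 15 centres. **Assumptions not in the document:** the nine added centres recruit at the average of the first six, and all 15 are open for the full 3 years.

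**1. The target of 506 reproduces.** The hazard ratio is ln(0.80)/ln(0.70) = 0.626. The article states no significance level; two-sided 5% is assumed. With 80% power, Freedman's formula gives 149 events. Exponential survival with uniform 3-year accrual and 5 further years of follow-up gives an average event probability of 0.3105. Then 149/0.3105 = 479.9, and dividing by 0.95 for loss gives 505.1, hence 506. The target is taken as sound.

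**2. What the feasibility figures imply.** Eligible in 18 months: 200 × 1.5 = 300.
- At 20%: 60 patients, 60/18 = 3.33 per month. The planned 60 is therefore the 20% figure.
- At 25%: 75 patients, 75/18 = 4.17 per month.

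**3. Projection to the main trial.** Feasibility exposure is 6 × 1.5 = 9 centre-years; main-trial exposure is 15 × 3 = 45 centre-years.

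| Uptake | Per centre-year | 15 centres, 3 years | Months to 506 with 15 centres | Centres for 506 in 3 years |
|---|---|---|---|---|
| 20% | 60/9 = 6.67 | 300 | 60.7 | 25.3 (so 26) |
| 25% | 75/9 = 8.33 | 375 | 48.6 | 20.2 (so 21) |

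**4. What 506 requires.** 506/(15 × 36) = 0.937 per centre-month. Times six centres, that is 5.62 per month, or 101 patients in 18 months. At 300 eligible, 101.2/300 = 34% uptake.

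**5. Consequence of stopping at 300.** Expected events are 300 × 0.95 × 0.3105 = 88.5. By Schoenfeld's approximation, ln(1/0.626) × √(88.5/4) − 1.96 = 0.24, so power is about 60%. The same approximation gives about 82% at 506.

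**6. How much better the added centres would have to be.** At 20% the first six contribute 6.67 × 6 × 3 = 120. The other nine must supply (506 − 120)/(9 × 3) = 14.3 per centre-year, about 2.1 times the yield of the first six.

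**7. Volume does not enter the ratio.** With 150 eligible in 18 months instead of 300, 30 randomised still meets 20%. The rate is 30/18 = 1.67 per month, projecting to 30/9 × 45 = 150 of 506.

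**The case against.** The strongest reply is that the 20% is a necessary condition and is nowhere called sufficient. The first guideline depends on volume, and a study projecting to 150 of 506 ought to fail it whatever its uptake. This stands. A reader might infer that the plan would return a go for a main trial that cannot be recruited; the document does not support that, because meeting the ratio is only one of two requirements. What remains is that the first guideline has no cut-off. The document's figures support 3.3, 4.2 or 5.6 per month as its meaning, so an observed 4 per month could be called adequate or inadequate.

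A reader might also infer the reverse error: that the 20% condition would reject a main trial with ample recruitment. This is arithmetically possible. With 600 eligible in 18 months and 17% randomised, 102 patients project to 510. But it needs more than about 506 eligible in 18 months, or 337 a year. That is 34% of the 1000 diagnoses, against the 20% assumed. It is a remote case and carries no weight here.

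It is also fair to say that uptake deserves its own gate. Willingness to be randomised between surgery and bladder preservation is the central uncertainty, and low volume can be met by adding centres in a way that refusal cannot. This is why the uptake condition should stay.

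Finally, the article condenses a fuller protocol that may hold a rate threshold. That cannot be excluded. However, the article presents its progression guidelines as defined, and the mismatch between 20%, 25%, 60 patients and 506 lies within its own text.

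**Conclusion.** The point holds in a limited form. The one numeric progression condition is independent of eligible volume, the volume-related guideline is unquantified, and neither primary outcome has a pass mark. At the plan's own 200 eligible per year, meeting the 20% mark exactly projects to about 300 of 506 patients in 3 years, and the 25% planning figure to about 375. The rate needed at the six centres is about 5.6 per month, against 3.3 planned.

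The projections rest on equal yield per centre and on 15 centres open throughout. Staggered opening would worsen them; larger added centres would improve them, but at 20% uptake those centres would need roughly double the yield, which the document does not claim. The matter should be corrected because the progression decision is the study's main product. It does not affect the validity of the data being collected.

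**What to change.** In the progression criteria, keep the 20% uptake condition and add a numeric criterion on patients randomised per centre per month, calculated as main-trial N / (main-trial centres × accrual months). Report eligible patients per year against the assumed 200 alongside it. Fix the mark before the recruitment data are judged against it.

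Do not insert the present result, 0.937 per centre-month (5.6 at six centres), without further change: a study that met its target of 60 in 18 months would then fail automatically. First reconcile the Sample size and progression sections on 20% versus 25%, 60 in 18 months, nine added centres and 3 years. Sixty in 18 months is 60/(6 × 18) = 0.556 per centre-month, so 506 patients need 506/0.556 = about 911 centre-months. That is about 61 months with 15 centres, or 26 centres over 36 months. The alternative is to state and justify a higher yield for the added centres. If the accrual period changes, recompute 506 as well, since it assumes 3 years.

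The cost is a rewording of two sections. Screening, eligibility and randomisation counts are already to be recorded and summarised. The drawback is that the main trial will look larger or slower than now stated, unless a higher yield can be justified.

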### Qualitative substudy

There are two qualitative studies. The first was undertaken prior to the start of the RCT to identify a priori the barriers to recruitment from the perspectives of patients and staff to inform the development of a bespoke training package for staff^41^ (see online supplementary file 1). A second qualitative study is embedded into the RCT trial to understand patients’ views and experiences of the treatments and explore patients’ acceptability of the study and recruitment processes:

### Qualitative substudy **objectives**

To gauge patients’ understanding of the study and their views on the recruitment process.To qualitatively explore patient’s acceptability of the study to assist in optimisation of recruitment strategies employed for the definitive trial.To explore reasons for participation and non-participation of eligible patients.To understand patients’ experience of the randomisation process on decision making.To understand why people refuse to participate or do not take up allocated treatment.Patient understanding of study materials, that is, do patients understand what will happen if they take part and do they understand what they are being randomised to.Acceptability of study procedures.Acceptability of randomisation.

### Qualitative substudy overview

In order to examine the views and experiences of patients with BC, we will conduct in-depth semistructured interviews with patients approached to take part in the trial. Qualitative findings will help illuminate the acceptability of trial processes and explore barriers to uptake.

Recruitment to RCTs with very different treatment arms can be difficult, and recruitment to trials involving surgery is particularly challenging.^42^ Trials present practical and methodological challenges, including difficulties in recruitment, randomisation and lack of clinical equipoise.^43^ Understanding why patients do or do not participate in trials is important, and clinical trials have recently begun to incorporate a qualitative component to address these issues. These studies have been able to successfully identify aspects of the trial design that hindered recruitment and identify possible solutions.^42 44^

### Qualitative substudy design

All eligible patients will be asked to complete a questionnaire to gauge their understanding of BRAVO and their views on the recruitment process. We will collect data from patients who decline the study, who consent but refuse allocation and who consent and accept allocation. A short questionnaire will be given to seek patient views on the recruitment process and to ask if participants would be willing to provide detailed feedback by face-to-face or telephone interview. A purposive sample of 15 patients will be selected for interview. Written consent will be taken prior to the interview and a flexible topic guide developed in conjunction with patient and public involvement (PPI) representatives, clinical colleagues and informed by the literature used to assist questioning. The topic guide will be devised to ensure that the key issues are covered but do not dictate data collection and will be flexible enough to elicit participants’ own experiences and views of the trial as well as issues unanticipated by the interview team. Interviews will be audio-recorded, transcribed and anonymised to protect confidentiality. With their consent, participants may be contacted after the interview to answer questions that may emerge during the analysis or to explore issues that emerged in the interviews in more depth.

### Qualitative substudy data analysis

Qualitative data will be analysed by the qualitative researcher. Interview transcripts will be checked for accuracy and then managed using NVivo qualitative data analysis software (QSR International, Daresbury, UK), which aids the indexing of qualitative data. Analysis will start during data collection and will inform later data collection; for example, emerging themes may identify new questions to explore in later interviews. The data will be analysed using thematic analysis^45 46^ using an inductive (bottom up) approach to identify and analyse patterns across the dataset using constant comparison methods.^47 48^ Inductive coding will follow using a line-by-line coding approach, with codes assigned to segments of data that provide insight into participants’ views of the trial. An initial coding frame will be developed from the first interviews and will be modified, if necessary, as the analysis develops. A subset of transcripts will be independently coded by another member of the team and compared with ensure consistency. Any discrepancies will be discussed with the research team and resolved to achieve coding consensus. The data will be examined for negative cases, and the reasons will be explored by comparison with the overall dataset.

### Data monitoring

Trial supervision includes a core project team, a trial management group (TMG) and an independent trial steering committee (TSC). For a feasibility study of this nature and duration, a separate data monitoring and ethics committee is not required; rather; TSC adopts a safety monitoring role and will review safety issues if this becomes necessary. Data will be monitored for quality and completeness by the Clinical and Translational Research Unit (CTRU). Missing data (except individual items collected via questionnaires) will be chased until received, confirmed as not available or the trial is at analysis. Any protocol changes will be disseminated by CTRU to the relevant parties.

### Trial organisation and administration

The trial was developed by the BRAVO TMG. The trial is funded by Yorkshire Cancer Research and is sponsored by the Sheffield Teaching Hospitals NHS Trust (Clinical Research Office, Royal Hallamshire Hospital, [name]), coordinated by CTRU, University of Leeds, and is registered (ISRCTN12509361). The trial will be conducted in accordance with the principles of Good Clinical Practice (GCP) in clinical trials, as applicable under UK regulations, the NHS Research Governance Framework and through adherence to CTRU standard operating procedures. CTRU/sponsor have systems in place to ensure that serious breaches of GCP or the trial protocol are identified and reported. Ethical approval has been obtained from the National Research Ethics Service Committee Yorkshire & Humber–South Yorkshire (reference no. 16/YH/0268). Any on-site source data verification carried out by CTRU is not independent from sponsor. Sheffield Teaching Hospitals NHS Trust will not be liable for negligent harm caused by the design of the trial. No additional compensation for clinical negligence will be provided for trial participants over that which is available to NHS patients. All identifiable information collected during the course of the study will be kept strictly confidential and not transferred outside of the research team. Patient name (via consent form), email address and telephone number will be collected when a patient is randomised into the study, but all other data collection forms that are transferred to or from the CTRU will be coded with a study number and will include two patient identifiers, usually the patient’s initials and date of birth. Both electronic and paper data will be held in a secure locations with restricted access.

## Discussion

The 2015 NICE BC guidelines identified the comparison between mBCG and RC as one of their highest research priorities.^21^ This reflects the importance of this question but does not address how randomisation between two very different treatment options should occur or whether such a comparison is possible. Within this feasibility study, we are attempting to understand, address and develop methodology to allow such a comparison. This will require several key issues to be addressed. First, it is clear from other surgical versus non-surgical treatment trials^49^ that the most important element for RCT recruitment is keeping equipoise when discussing the treatment options by medical and nursing staff. While previous studies used research nurses to keep equipoise, this is not viable across many centres within the current research funding climate. In an attempt to replicate this model, we ran a number of educational days to train relevant medical and nursing staff about the importance of equipoise and to discuss their beliefs about HRNMIBC. All staff had opinions about the efficacy of BCG and QoL with RC, and so it was important to discuss these in an open forum to challenge these views and use evidence to dispel prior beliefs. We proposed a six-stage consultation plan to help staff keep patients at equipoise and so facilitate trial entry and treatment acceptance.^50^ Within this feasibility study, we will determine if this approach is possible and successful. Second, UK data do not accurately identify the number of patients with HRNMIBC, what proportion of these are suitable for both RC and mBCG and how many of these would accept randomised treatment options. Within this feasibility study, we will establish accurate data about the number of eligible cases across this population and understand what proportion accepts their randomised treatment allocation. We will use these findings to power the phase III comparative study. Finally, there are very few reliable data about QoL with mBCG and none that compare this directly to RC. Within this study, we will produce these data within 60 patients (30 for each arm) and so allow this endpoint to be modelled for the larger phase III study.

## Ethics and dissemination

The study has ethical approval from Research Ethics Service Committee Yorkshire & Humber–South Yorkshire (reference no. 16/YH/0268). The results of the study will be published in peer-reviewed publications and will be presented at relevant national and international conferences. We will work with our patient panel of BC survivors to develop lay reports to disseminate research findings to patient groups and the clinical teams at participating sites.

### Availability of data

CTRU will control the final trial dataset and any requests for access will be reviewed by TMG and TSC, subject to existing contractual arrangements with the funders. The protocol, sample case report forms and participant information are available on a case-by-case basis as agreed by TMG, on request to the corresponding author.

